### Outcome Measures

The primary outcome will be the change in the incidence of stroke comparing the 5-year preintervention period with the 2-year period following the start of the intervention, as recorded in the Programme de Médicalisation des Systèmes d’Information (PMSI) database. Secondary outcomes will include changes in incidence of ACS [28], TIA [29], PAD [30], aneurysm, and ESRD [31] (*insuffisance rénale terminale* [IRT]), as well as all-cause cardiovascular mortality within 1, 2, and 3 years after the intervention. ACS refers to a spectrum of urgent cardiac conditions caused by a sudden reduction in blood flow to the heart muscle due to a partial or complete blockage of the coronary arteries. This group of conditions includes unstable angina and non–ST-elevation myocardial infarction (NSTEMI), both of which require prompt diagnosis and individualized treatment strategies to prevent further cardiac damage and improve patient outcomes.

ESRD represents the final and most advanced stage of chronic kidney disease, defined by a severely reduced GFR of less than 15 mL/min/1.73 m^2^. At this stage, patients require kidney replacement therapy, which includes either long-term dialysis or kidney transplantation. ESRD is a chronic condition that typically arises in the context of long-standing comorbidities, notably hypertension.

PAD is a circulatory condition characterized by the narrowing or blockage of peripheral arteries, most commonly in the lower limbs, due to the buildup of atherosclerotic plaques. This reduced blood flow can lead to symptoms such as leg pain during walking (claudication), numbness, or even tissue damage in severe cases. Importantly, PAD is not confined to the extremities; it reflects a systemic atherosclerotic process that affects multiple vascular beds. As such, PAD serves as a clinical marker for widespread vascular dysfunction and is strongly associated with an elevated risk of major cardiovascular events, including myocardial infarction and stroke.

Additional secondary end points will assess participants’ adherence to medical referrals, satisfaction with the program, the number of BP screenings completed, the number of new or rediagnosed hypertensive cases, and changes in antihypertensive prescription patterns using health insurance data. Outcome assessments will be based solely on administrative records and structured questionnaires, minimizing subjectivity and measurement variability.

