The primary approach uses the chi-square test; approximately 350 patients with stroke are admitted annually to the Centre Hospitalier de Cayenne, with 68% (n≈238) occurring among socioeconomically precarious patients. Assuming the intervention leads to a 30% reduction in stroke incidence within this population—consistent with previous international interventions—a postintervention count of approximately 167 strokes per year (a reduction from 238) is anticipated. To detect this effect with 90% power at a 5% significance level (α=.05) using a 2-sided chi-square test comparing proportions before and after the intervention, a minimum of 367 cumulative postintervention stroke cases over a 2-year period is required.

Second, a segmented regression (ITS) analysis will be used to complement the chi-square test by examining both immediate level changes and slope changes after the intervention. On the basis of 60 monthly preintervention observations (5 years) and 24 monthly postintervention observations (2 years), and assuming autocorrelation (ρ=0.3-0.5) typical of health administrative data, this design provides adequate power (>80%) to detect a change in slope corresponding to a 20% to 30% reduction in incidence, assuming a baseline coefficient of variation of 15% to 20% in monthly stroke counts.

The chi-square test provides a straightforward test of the primary hypothesis, while ITS analysis accounts for underlying temporal trends and potential confounders, offering a more nuanced understanding of intervention effects. Both analyses will be reported, with ITS serving as the primary confirmatory analysis and the chi-square test as a sensitivity check.

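### The required minimum of 367 post-intervention strokes exceeds the roughly 334 expected under the plan's own 30% effect and does not follow from its stated inputs

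*Protocol article*

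**What the plan says.** All the figures are in the sample-size paragraphs that close the Statistical Analysis section of the protocol article.

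- Baseline: "approximately 350 patients with stroke are admitted annually to the Centre Hospitalier de Cayenne", "with 68% (n≈238) occurring among socioeconomically precarious patients".
- Effect: "Assuming the intervention leads to a 30% reduction in stroke incidence within this population", so that "a postintervention count of approximately 167 strokes per year (a reduction from 238) is anticipated".
- Test and error rates: "90% power at a 5% significance level (α=.05" (the bracket closes after the alpha value), "using a 2-sided chi-square test comparing proportions before and after the intervention".
- Result: "a minimum of 367 cumulative postintervention stroke cases over a 2-year period is required".

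Outcome Measures fixes the comparison as "comparing the 5-year preintervention period with the 2-year period following the start of the intervention".

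The next sample-size paragraph gives a separate power statement for the interrupted time series (ITS): 60 monthly points before and 24 after, autocorrelation 0.3 to 0.5, a coefficient of variation (CV) of 15% to 20% in monthly counts, and more than 80% power for a 20% to 30% reduction. The section closes by making ITS the confirmatory analysis and the chi-square test a sensitivity check.

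**The concern.** The anticipated count and the required count describe the same population, effect and 2-year period, and they disagree. A minimum number of post-intervention events is also an awkward target for a prevention study, because the better the intervention works, the fewer events there are. As written, a result exactly on the planning assumption falls short of the published minimum, and a weaker effect satisfies it.

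The stakes are in how the results are read. The 367 is the only event-count requirement in the article, and the text calls this calculation the primary approach to sample size. A reader who holds the observed count against it would be misled about whether the study met its design. That reader is also given neither the real nominal power of the before-after comparison nor the smallest reduction it can detect.

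**Working it through.** **Inputs.** 350 strokes a year, 68% in precarious patients, rate ratio 0.70, two-sided alpha 0.05, power 0.90 (Statistical Analysis); 5 years before, 2 years after (Outcome Measures). The sample-size text gives no denominator. Where a proportion is needed I assume the 50,000 adults given in Intervention or Treatment; with events this rare the choice hardly matters.

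**Step 1: the plan's own counts.** 350 × 0.68 = 238 a year. 238 × 0.70 = 166.6, rounded to 167. Over 2 years this is 2 × 167 = 334 (333.2 unrounded). With no effect, 2 × 238 = 476. Over 5 baseline years, 5 × 238 = 1,190.

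**Step 2: compare with 367.** 367 − 334 = 33. 367/476 = 0.771, a 22.9% reduction. For a Poisson count with mean 334, P(X ≥ 367) ≈ 0.04.

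**Step 3: try to reproduce 367.** Post-intervention events needed on the log-rate scale, with k = pre/post length:

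E = (1.96 + 1.2816)² × (1 + 0.7/k) / (ln 0.7)², with (1.96 + 1.2816)² = 10.507 and (ln 0.7)² = 0.1272

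- k = 1: 10.507 × 1.70 / 0.1272 = 140
- k = 2.5: 10.507 × 1.28 / 0.1272 = 106

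The pooled two-proportion formula gives 140 for equal windows (145 with continuity correction). For 5:2 windows it gives 100 at 238 against 167, or 98 at a rate ratio of exactly 0.70. Schoenfeld and Freedman event formulas give 331 and 338 events in total, not after the intervention. So 367 is about 2.6 times the equal-window requirement (367/140) and 3.5 to 3.7 times the 5:2 requirement (367/106, 367/98).

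**Step 4: near matches.** Each needs a different quantity or an unstated step.

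- 5:2 windows with continuity correction: 366.8 cases, but *before* the intervention (about 103 after).
- All strokes, 350 falling by 71 to 279 a year, equal windows: 10.507 × (1 + 0.797) / (ln 0.797)² ≈ 367 after the intervention on the log-rate scale; other formulas give 363 to 371.
- A 10% inflation: 334 × 1.10 = 367.4, or 331/0.9 = 368.

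**Step 5: nominal power at the plan's counts.** z = 0.357 / √(1/1,190 + 1/333) = 5.75, so power exceeds 99.9%. With only 2 baseline years (476 against 333) it is about 99.9%.

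**Step 6: what 90% power would detect.** Solve −ln(RR) = 3.2415 × √[f × (1/1,190 + 1/(476·RR))], where f is the variance relative to independent Poisson months.

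- f = 1: RR = 0.83.
- Plan's CV and autocorrelation: the monthly mean is 238/12 = 19.83, so variance/mean = CV² × 19.83 = 0.45 (CV 15%) to 0.79 (CV 20%). Under AR(1) the long-run factor (1 + ρ)/(1 − ρ) is 1.86 (ρ = 0.3) to 3.0 (ρ = 0.5). Hence f = 0.83 to 2.38 and RR = 0.84 to 0.74.
- Sensitivity: a CV of 15% to 20% is below the Poisson value at this mean (1/√19.83 = 22.5%). If monthly variance is at least Poisson, f = 1.86 to 3.0 and RR = 0.77 to 0.71.

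**The case against.** The strongest reply is that 367 controls nothing. The windows are fixed, strokes come from routine hospital data, field work has ended, and no rule for stopping, extension or interpretation depends on the figure. It sizes a test that the plan itself calls a sensitivity check. All of that stands, and it limits the severity.

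The reply can also say that a journal article condenses the full protocol, so the missing formula, ratio and inflation may be written there, and that the near matches make a mislabelled figure plausible. That is fair as far as the missing detail goes, and it is why clarifying the figure is as acceptable as withdrawing it. It does not remove the contradiction. The article ties 367 to the fall from 238 to 167 in precarious patients, and no omitted detail makes 334 events meet a minimum of 367. On the all-stroke reading about 2 × 279 = 558 cases would be expected and 367 would be within reach, but that is not the comparison described.

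A reader might go further and infer that the study is too small, that the target can never be met, or that this is the only sizing given. The documents support none of these. Power at the planned counts is well above 90%; 334 is an expectation, so 367 or more remains possible; and the ITS power statement is a second sizing.

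**Conclusion.** The point holds as an arithmetic contradiction. The stated minimum exceeds the count expected under the plan's own alternative by 33 events, and it does not follow from the stated inputs, which need about 140 post-intervention events (equal windows) or about 98 to 106 (5:2). The first part rests only on the article's figures. The second rests on standard two-sample formulas and barely depends on the assumed denominator.

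It is a correction to a stated figure and no threat to the trial's power. A reader might also infer that autocorrelation pushes the assumed 30% reduction to the edge of what can be detected. With the plan's own CV and autocorrelation it does not: a simple before-after comparison detects a reduction of about 16% to 26% at 90% power, and even with at least Poisson variance the limit is about 29%. These limits assume AR(1) errors and no underlying trend. They are not the power of the segmented regression, which must also estimate level and slope.

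**What to change.** Rewrite the first sample-size paragraph.

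- Withdraw 367 as a minimum. Alternatively keep a corrected figure and say which cases it counts (before or after; precarious patients or all strokes), the formula, the pre:post ratio and any inflation, and reconcile it with 334.
- State the size as what is actually fixed: 60 months before and 24 after, with about 1,190 expected events before and, after, 476 under no effect or 333 under a 30% reduction.
- Give the rate ratio detectable at 90% power using the plan's CV and autocorrelation (about 0.84 to 0.74 for a simple before-after comparison, AR(1), no trend), and say whether the CV refers to the precarious-patient series.
- Say in the same paragraph that this calculation supports the chi-square sensitivity check and that the confirmatory ITS has its own power statement.

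The cost is one paragraph of recalculated text. No new data and no change to the design or analyses are needed.

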### Statistical Analysis

Statistical analyses will be conducted using Stata (version 19; StataCorp). Continuous variables will be described using means and SDs when normally distributed; for skewed distributions, medians and IQR will be reported. Normality will be assessed using visual inspection of histograms and quantile-quantile plots and confirmed with the Shapiro-Wilk test.

Comparisons of continuous variables between groups (eg, before vs after the intervention and intervention vs control regions) will be performed using the Student *t* test or the Mann-Whitney *U* test, as appropriate. The Student *t* test is a statistical method used to determine whether the means of 2 independent groups are significantly different from each other. It assumes that the data in each group are approximately normally distributed and that the variances are equal or similar.

Categorical variables will be summarized as absolute frequencies and percentages. Between-group comparisons will be conducted using chi-square tests or Fisher exact tests.

All statistical comparisons will be 2-sided, and results will be considered statistically significant if *P*<.05. Corresponding 95% CIs will be reported for all estimated parameters.

The primary outcome analysis will assess the difference in stroke incidence before and after the 2-year intervention period among residents of precarious neighborhoods within the CACL of French Guiana. Stroke incidence, derived from PMSI hospitalization data, will be compared across the 2 periods using the chi-square test. To evaluate temporal trends and detect structural breaks attributable to the intervention, segmented regression of interrupted time series (ITS) [33] data will be applied. The ITS model will estimate the immediate change in level and the change in slope after the intervention, while adjusting for autocorrelation and seasonality as necessary based on model diagnostics (Figure 3).

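### The power of over 80% stated for the confirmatory interrupted time series is not met across the plan's own inputs, and the assumed monthly variability is too low for 238 strokes a year

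*Protocol article*

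**What the plan says.** The closing paragraphs of Statistical Analysis in the Protocol article give two sample-size approaches and name the ITS as the primary confirmatory analysis, with the chi-square test as a sensitivity check. The conclusion on the ITS is that "this design provides adequate power (>80%) to detect a change in slope corresponding to a 20% to 30% reduction in incidence". Three inputs are given for it. The number of time points is 60 months before and 24 months after the start of the intervention. Dependence between months enters through the words "assuming autocorrelation (ρ=0.3-0.5) typical of health administrative data". Variability is covered by the phrase "assuming a baseline coefficient of variation of 15% to 20% in monthly stroke counts". The model is described earlier in the same section: "The ITS model will estimate the immediate change in level and the change in slope after the intervention". Tests are two-sided at 5%.

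The first approach supplies the event count: about 350 stroke admissions a year, "with 68% (n≈238) occurring among socioeconomically precarious patients", expected to fall by 30% to about 167 a year. The primary analysis is placed in residents of precarious neighborhoods. The article does not say how a slope change translates into a 20–30% reduction.

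**The concern.** Two things do not fit together. First, a segmented regression with separate level and slope terms estimates the slope change from only 24 post-intervention months, and autocorrelation of 0.3–0.5 reduces the information further. Power above 80% for a reduction as small as 20% looks high for that model. Second, about 20 events a month cannot vary by as little as 15–20%, because random counting variation alone exceeds that.

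This figure supports the study's main inference. If it is too high, a non-significant slope change could be taken as an adequately powered negative result when a true 20% reduction would often have been missed.

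**Working it through.** **Inputs from the article:** 60 pre- and 24 post-intervention months; ρ = 0.3–0.5; CV = 15–20%; reduction of 20–30%; two-sided α = 0.05; intercept, pre-trend, level change and slope change in the model; 238 (precarious patients) or 350 (all) strokes a year.

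**Assumptions added:** AR(1) errors, CV read as marginal SD divided by baseline mean, known ρ, flat baseline, linear scale with constant SD.

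**Step 1. Standard error of the slope change.** Counts are scaled by the baseline mean. X has columns 1, t, post and (t − 60) after month 60; V has elements CV²·ρ^|i−j|. The SE is the square root of the slope-change element of (X′V⁻¹X)⁻¹.

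**Step 2. Slope implied by the reduction.** The mean of months 1 to 24 is 12.5.
- Average reading: 0.20/12.5 = 0.0160 and 0.30/12.5 = 0.0240 per month. The line then ends at 24 × 0.0160 = 38% or 24 × 0.0240 = 58% below baseline.
- Month-24 reading: 0.20/24 = 0.0083 and 0.30/24 = 0.0125 per month.

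**Step 3. Power** = Φ(slope/SE − 1.96); the other tail is negligible.

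| ρ | CV | SE per month | Average 20% | Average 30% | Month-24 20% | Month-24 30% |
|---|---|---|---|---|---|---|
| 0.3 | 15% | 0.00592 | 77% | 98% | 29% | 56% |
| 0.5 | 15% | 0.00702 | 63% | 93% | 22% | 43% |
| 0.3 | 20% | 0.00790 | 53% | 86% | 18% | 35% |
| 0.5 | 20% | 0.00936 | 40% | 73% | 14% | 27% |

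Worked cell (ρ 0.5, CV 20%, average 20%): 0.0160/0.00936 = 1.71; Φ(1.71 − 1.96) = 40%.

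The reduction detectable with 80% power is 2.80 × SE × 12.5 = 21–33% as an average, or 2.80 × SE × 24 = 40–63% at month 24.

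**Step 4. Can the stated figure be reproduced?** Not with the planned model. Of the slope models tried, only one with neither level term nor pre-intervention trend, on the average reading, exceeds 80% at every corner (86% to nearly 100%). The article commits to a level term and to control of the underlying trend.

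**Step 5. Minimum CV.** For Poisson counts, CV = 1/√(monthly mean).
- 238/12 = 19.83 a month: 1/√19.83 = 22.5%.
- 350/12 = 29.17 a month: 1/√29.17 = 18.5%.
- A CV of 20% needs 12/0.20² = 300 strokes a year; 15% needs 12/0.15² = 533.

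**Step 6. Power with CV 22.5%, average reading.** With ρ = 0 the SE is 0.00683 and power is 65% (20%) and 94% (30%). With ρ = 0.3–0.5 the SE is 0.00887–0.01051 and power is 33–44% (20%) and 63–77% (30%). These last values are upper limits on this method: Poisson variation is uncorrelated from month to month, so autocorrelation of that size requires further variance and a CV above 22.5%.

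**The case against.** **The effect is a whole-period change.** A reader might infer from the month-24 figures that the design cannot detect the effect it names. The article does not support that. It expresses the effect as 238 falling to 167 strokes a year, and Principal Anticipated Findings speaks of the 2-year period against the 5-year baseline. On that reading a 30% reduction has more than 80% power at three of the four corners. This stands, and it is why the average reading leads here.

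**The scale matters.** On a log scale with constant CV, an average reduction of 20% or 30% needs a log-slope of 0.0185 or 0.0303 per month (the mean of exp(−bk) over k = 1 to 24 is then 0.80 or 0.70). Divided by the SEs in the table, these give 51–88% and 90% to over 99%. The 30% claim then holds on the stated inputs and the 20% claim still fails at three corners. That version keeps the CV constant as counts fall, so it departs further from the Poisson minimum.

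**The CV criticism depends on the series.** The article does not say which monthly counts it means, and Primary Objective refers to adults in the whole agglomeration. At 350 a year a CV of 18.5–20% is possible, so the whole range is ruled out only for the 238 series. Even then, 15% fails.

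**Consequences are limited.** Fieldwork ended in September 2025, so no sample-size decision can change, and 95% CIs are promised for all estimates. The calculation method may be in the full protocol. None of this makes the stated figure correct for the inputs given.

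**Conclusion.** Wrong as written. In the planned level-plus-slope model, power above 80% does not hold across the stated inputs on either reading of the reduction. The main shortfall is at 20%: 40–77% as a 24-month average. At 30% the average-reading range of 73–98% mostly meets the claim, so the finding is not that the design is unable to detect its planning effect. The assumed CV lies wholly below the Poisson minimum for the article's own 238 strokes a year, and its lower end is impossible for 350 as well.

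The exact percentages rest on AR(1) errors, known autocorrelation, a flat baseline and a linear scale. The failure at 20% also appears on the log scale. The CV result needs only that monthly counts vary at least as much as Poisson counts.

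**What to change.** In the sample-size text of Statistical Analysis, replace the statement of power above 80% with the power, or preferably the minimum detectable effect, of the planned level-plus-slope model. Recompute it from the observed 60 pre-intervention months of the series that will be analyzed, with variance no smaller than Poisson and autocorrelation estimated from that series. Name the series and the model scale, and state whether 20–30% is the average over 24 months or the reduction at month 24.

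Using only pre-intervention months keeps the recalculation independent of the result. The cost is a short calculation on data the analysis needs anyway and a few sentences of text; design and conduct do not change. The stated power will probably be less favorable, especially at 20%.

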### Objectives

#### Primary Objective

The primary objective is to determine whether a community-based hypertension screening and referral intervention delivered by trained health mediators is superior to standard health service delivery in reducing the incidence of stroke (*accidents vasculaires cérébraux* [AVC]) over a 2-year period, compared to the 5-year preintervention period, among adults residing in the CACL region of French Guiana.

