### Intervention or Treatment

The intervention will consist of a comprehensive, community-delivered hypertension screening and education program. It will be implemented by 12 trained health mediators organized into 3 teams of 3 to 4 mediators each. The protocol stipulates that each mediator can screen approximately 10 people per day, representing a target of 2000 adults per month. These mediators, certified through a university-level diploma in health mediation or with equivalent field experience, will engage directly with residents in all precarious neighborhoods within the CACL. Each neighborhood will receive at least 1 intervention visit during the 24-month intervention period. The number of visits per neighborhood will be determined based on population size and accessibility. The goal is comprehensive coverage of an estimated population of 50,000 adults in the target neighborhoods.

To maximize reach, each visit will last 1 to 2 days, with mediators establishing fixed screening posts and conducting door-to-door outreach. The quantification of coverage will not be based solely on the number of individuals screened but on the number of neighborhoods fully investigated by the mediators. The intervention will be considered complete for a neighborhood when the minimum number of planned visits has been conducted, when mediators have systematically covered all streets or sectors through door-to-door approaches, or when repeated visits yield diminishing returns.

Given population mobility and the informal nature of precarious settlements, we acknowledge that precise denominator estimation is challenging. Mediators will set up mobile stations or conduct home visits to measure BP triadically according to European guidelines, provide personalized health education focused on hypertension and lifestyle modification, assess health insurance coverage, and guide participants with elevated BP to appropriate health care professionals or social services (eg, general practitioners or the PASS unit). Follow-up will include a structured telephone call 3 months later to assess completion of the medical referral process.

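### The before/after chi-square has no trend term, so it does not test the primary hypothesis and is a poor sensitivity check on the confirmatory interrupted time series

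*Protocol article*

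**What the plan says.** The Primary Objective asks whether the programme "is superior to standard health service delivery in reducing the incidence of stroke", set against a 5-year period before the intervention. That is a question about what incidence would have been without the programme.

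The primary-outcome paragraph of Statistical Analysis answers first with a two-period comparison: "Stroke incidence, derived from PMSI hospitalization data, will be compared across the 2 periods using the chi-square test". Segmented regression follows, with terms for level and slope change.

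The sample-size text at the end of that section again puts the two-period test first: "The primary approach uses the chi-square test; approximately 350 patients with stroke are admitted annually". Its closing paragraph states: "The chi-square test provides a straightforward test of the primary hypothesis, while ITS analysis accounts for underlying temporal trends". The last sentence then ranks the two analyses, "with ITS serving as the primary confirmatory analysis and the chi-square test as a sensitivity check", and says that both will be reported.

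Strengths and Limitations accepts that secular trends and changes in health care access could move the outcome independently of the intervention. The article describes no trend term or comparison series for the chi-square.

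**The concern.** The chi-square and the primary objective have different null hypotheses. The objective's null is that incidence after the start is what standard care would have produced. The chi-square's null is that average incidence is equal in two pools, 60 months before and 24 months after. With any background drift, or any growth of the population that the denominator misses, the second null can be false while the first is true.

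A sensitivity check should put the same question under different assumptions. This one removes the trend adjustment that is the article's reason for using ITS. Under a downward drift it would produce a small P value beside the ITS result and appear to corroborate a reduction that would have happened anyway. Under an upward drift it could appear to contradict a real effect. This is a bias in what is tested: it remains if every month is independent and the standard error is correct.

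**Working it through.** **Inputs from the Protocol article.** Annual stroke admissions 350, "with 68% (n≈238) occurring among socioeconomically precarious patients". Planned effect: "Assuming the intervention leads to a 30% reduction in stroke incidence within this population". Expected effect 20% to 30% (Principal Anticipated Findings). Periods of 5 and 2 years; two-sided 5% level.

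**Assumed, because the article gives no figure.** A constant multiplicative trend g per year, a constant denominator and independent Poisson months.

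**The plan's own figures.** 350 × 0.68 = 238 and 238 × 0.70 = 166.6, about 167 a year, so both reproduce. The stated minimum of 367 post-start strokes does not. A Poisson rate-ratio calculation at 90% power and 5:2 person-time gives (1.960 + 1.282)² / (ln 0.70)² × (1 + 0.70 × 2/5) = 10.51 / 0.1272 × 1.28 ≈ 106. That is a separate matter, and nothing below uses 367.

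**Hand check.** The period midpoints are 2.5 and 6 years from the start of the series, 3.5 years apart. With no trend the expected counts are 5 × 238 = 1,190 and 2 × 238 = 476. The SE of the log rate ratio is √(1/1,190 + 1/476) = 0.054. A drift of 3% a year shifts the log ratio by about 3.5 × 0.03 = 0.105, which is 0.105 / 0.054 ≈ 1.9 SE. That alone nearly reaches the 1.96 threshold.

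**Full calculation.** Fix the pre-period total at 1,190. The post-start expectation is x = 1,190 × [sum of (1+g)^t over months 61–84] / [sum of (1+g)^t over months 1–60] × (1 − effect), with t in years. Then d = ln[(x/2)/(1,190/5)], SE = √(1/1,190 + 1/x), and P(significant reduction) = Φ(−1.96 − d/SE).

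| True effect | Trend per year | x | Rate ratio | d | SE | P(significant reduction) |
|---|---|---|---|---|---|---|
| none | 0 | 476.0 | 1.000 | 0 | 0.0542 | 2.5% |
| none | −1% | 459.5 | 0.965 | −0.035 | 0.0549 | 9.4% |
| none | −2% | 443.3 | 0.931 | −0.071 | 0.0556 | 24.7% |
| none | −3% | 427.5 | 0.898 | −0.107 | 0.0564 | 47.8% |
| 20% | 0 | 380.8 | 0.800 | −0.223 | 0.0589 | 96.6% |
| 20% | +2% | 408.0 | 0.857 | −0.154 | 0.0574 | 76.7% |
| 20% | +3% | 422.0 | 0.887 | −0.120 | 0.0567 | 56.6% |
| 30% | +3% | 369.2 | 0.776 | −0.254 | 0.0596 | 98.9% |
| 30% | +5% | 394.4 | 0.829 | −0.188 | 0.0581 | 89.9% |

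**Simulation check.** With no effect, the simulated 2×2 chi-square rejected (either direction) in 48, 26, 5.6, 26 and 51% of runs at −3, −2, 0, +2 and +3% a year. A Poisson segmented regression with trend, level change and slope change, tested jointly on the same series, rejected in 4.3, 5.0, 4.6, 4.9 and 5.4%. The excess therefore comes from the missing trend term.

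**The case against.** The strongest reply is rank. The closing sentence makes the ITS confirmatory and the chi-square subordinate, and the quoted sentence itself credits the ITS with handling trends. Comparisons with non-intervention areas are also planned. This stands. A reader might infer that the trial's confirmatory error rate is inflated; the documents do not support that, because the ITS sets it. What remains is that the chi-square is labelled a test of the primary hypothesis, comes first in the primary-outcome paragraph, heads the sample-size text and will be reported as a check.

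Other stronger readings also fail:

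- **The denominator.** A reader might take "we acknowledge that precise denominator estimation is challenging", in Intervention or Treatment, as an admission that the incidence denominator is unknown. It follows a discussion of screening coverage and of when a neighbourhood counts as complete. Population growth is a condition on which the chi-square depends, not a flaw that the article concedes.
- **Missed effects.** Power loss matters at a 20% reduction. At the planned 30% it is slight for mild trends: 98.9% at +3% a year.
- **Constancy over seven years.** The test's null is narrower than that: equal average incidence in the two periods.
- **No information at all.** Disagreement between the two analyses would still show that the conclusion depends on the trend adjustment.
- **An expected trend.** The article says that trends may operate; it gives no direction or size.

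**Conclusion.** The point holds, and it concerns the supporting evidence. The two-period chi-square answers the primary objective only without secular trend and with a stable or correctly measured population at risk, and the article itself allows that the first condition may fail. Of the two errors, false corroboration is the larger: about 9, 25 and 48% false significant reductions at declines of 1, 2 and 3% a year, against a nominal 2.5%. The opposite error is material only towards the lower end of the expected effect, where power for a 20% reduction falls from about 97% to 77% at +2% and 57% at +3% a year. Every figure away from zero trend depends on the assumed trend, on 238 strokes a year and on independent Poisson months.

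**What to change.** In the closing paragraph of the sample-size text, delete the clause that presents the chi-square as a test of the primary hypothesis, and end its role as a check on the ITS. Align the primary-outcome paragraph and the primary-approach label in the sample-size text, so that the ITS is the only test of that hypothesis. Report the crude before/after comparison as an unadjusted descriptive rate ratio with 95% CI and no P value.

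If a model-based sensitivity check is wanted, use a Poisson or negative binomial segmented regression of monthly counts with pre-intervention trend, level change and slope change, and a population offset where yearly estimates exist. A level-only model would not do. The article's ITS estimates level and slope, and neighbourhoods are reached over 24 months, so a gradual effect is plausible. In simulations of an effect ramping from 0 to 40% with no background trend, the level-only model had about 51–52% power, against 86–88% for the joint level-and-slope test.

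The cost is wording and at most one model on data already extracted. The report loses a simple significance test that is more powerful when there truly is no trend: about 97% for a 20% reduction, against 55–62% for the joint segmented test with a step effect and no autocorrelation. Results placed the primary analysis in April to May 2026. If it has been run, the change is one of reporting, and the report should say when the chi-square's role was changed.
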